## Abstract

**Background:**

Active transportation, such as walking and biking, is a healthy way for children to explore their environment and develop independence. However, children can be injured while walking and biking. Many cities make changes to the built environment (e.g., traffic calming features, separated bike lanes) to keep people safe. There is some research on how effective these changes are in preventing adult pedestrians and bicyclists from getting hurt, but very little research has been done to show how safe various environments are for children and youth. Our research program will study how features of the built environment affect whether children travel (e.g., to school) using active modes, and whether certain features increase or decrease their likelihood of injury.

**Methods:**

First, we will use a cross-sectional study design to estimate associations between objectively measured built environment and objectively measured active transportation to school among child elementary students. We will examine the associations between objectively measured built environment and child and youth pedestrian-motor vehicle collisions (MVCs) and bicyclist-MVCs. We will also use these data to determine the space-time distribution of pedestrian-MVCs and bicyclist-MVCs. Second, we will use a case-crossover design to compare the built environment characteristics of the site where child and youth bicyclists sustain emergency department reported injuries and two randomly selected sites (control sites) along the bicyclist’s route before the injury occurred. Third, to identify implementation strategies for built environment change at the municipal level to encourage active transportation we will conduct: 1) an environmental scan, 2) key informant interviews, 3) focus groups, and 4) a national survey to identify facilitators and barriers for implementing built environment change in municipalities. Finally, we will develop a built environment implementation toolkit to promote active transportation and prevent child pedestrian and bicyclist injuries.

**Discussion:**

This program of research will identify the built environment associated with active transportation safety and form an evidence base from which municipalities can draw information to support change. Our team’s national scope will be invaluable in providing information regarding the variability in built environment characteristics and is vital to producing evidence-based recommendations that will increase safe active transportation.

## Background

The Convention on the Rights of the Child states that “…children have the right to the highest attainable level of health and the right to a safe environment, free from injury and violence” [1]. Injuries are the most common cause of death and disability in children and youth and the majority of serious injuries are preventable [1]. Motor vehicle collisions (MVCs), including collisions with pedestrians and bicyclists, are the leading cause of paediatric injury and death. [name], a leading Canadian surgeon, and injury prevention expert has argued that: “By giving priority to automotive over pedestrian transportation, we have allowed road traffic to become the leading cause of death among our children” [2]. Until we start to address motor vehicle related pedestrian and bicycling injury via primary prevention strategies, such as modifying urban form (i.e., the built environment) to improve the support and safety of active transportation, these disturbing facts will not change. This research program focuses on the built environment and active transportation safety in children and youth. A built environment that promotes active transportation is necessary to meet both health goals (health promotion, injury prevention) and health equity goals (valuing children, reducing socioeconomic health and injury gradients).

Active transportation by children and youth increases their physical activity, which improves physical and mental health, maintenance of a healthy body weight, academic performance, motor skill development & physical literacy [3] [4]. Furthermore, physical activity habits and attitudes formed in childhood and adolescence are usually carried into adulthood [3–6]. However, only a third of Canadian children walk or bike to school, and longitudinal analyses indicate that the likelihood of using active transportation to school increases until age 10 and then decreases [7]. While it may not be possible for all children to walk to school, many Canadian parents who drive their children would allow them to use active transportation if traffic danger were reduced [8]. In particular, high perceived traffic danger on the school route lowers the odds of frequent walking by 47% [9]. As parents control the choices of school travel mode for children, it is essential to consider both actual and perceived collision risk in relation to the built environment. The analysis of these perceptions, both in children and their parents, leads to a better understanding of school travel choices. Active transportation rates are unlikely to improve without action to reduce traffic related injury risk.

Pedestrian and bicycling injuries are among the leading causes of death and hospitalization for Canadian children and youth [10]. Every year in Canada, 30 child pedestrians and 20 child bicyclists are killed and an additional 2400 child pedestrians and 1800 child bicyclists are injured [11, 12]. Based on 2010 data, child and youth pedestrian and bicycling injuries cost Canadians an estimated $266 million annually ([name]. Parachute, email communication, Dec. 22nd, 2015). Disability related to pedestrian and bicyclist-MVC is higher than that of other injury mechanisms (e.g., sports related injuries) six months post injury [13]. Research has shown a 4-fold increase in severe bicycling injury risk in children and youth with MV involvement [14]. Child specific studies are needed, as previous work shows that the location of child pedestrian injuries differs from other ages [15].

Many municipalities implement traffic calming strategies and broader infrastructure and built environment approaches, with the hope of shaping active transportation behaviours and road safety [16–18]. Modifying the built environment to promote active transportation can be costly and spark considerable debate at the municipal level. In fact, very little is known about the real efficacy of built environment interventions at promoting active transportation or preventing active transportation injuries [19]. In addition, children (who are still developing physically and cognitively) may have very different traffic infrastructure needs, compared with adults, due to different activity patterns, schedules and destinations. Built environment risk factors for active transportation injuries will also vary by age [15]. Parachute, Canada’s national injury prevention organization, maintains that children under age 10 are not physically and cognitively ready to bicycle on the road with motor vehicle traffic [20] and research supports this recommendation [14]. Child and youth pedestrians face similar challenges. Evaluation of initiatives to increase child and youth active transportation have generally focused on active transportation outcomes, such as participation rates, with little consideration of safety outcomes.

A systematic literature review indicated that bicycle-specific infrastructure (e.g., bike lanes and bike paths) have lower injury and crash risk, while multilane roundabouts without bike lanes, sidewalks, multi-use trails and major roads have higher risk [21]. Despite these important findings, unclear definitions and groupings of infrastructure types make it difficult to interpret injury and crash risk of specific infrastructure features. In addition, the range of infrastructure types studied to date is small compared with the range of existing roadway configurations [21]. Previous bicycling injury research has not adequately measured exposure to risk or controlled for potential confounders [21]. Recent emergency department (ED) based all-ages bicyclist injury research addressed many of these concerns and found significant associations between injury risk and certain infrastructure types (e.g., major streets with parked cars, construction, path obstructions, downhill grades, intersections) [22–24]. These approaches require focused application on child and youth bicyclists given their physical and cognitive differences from adults.

The effectiveness of traffic design interventions has often been examined for adult pedestrians [25, 26], but little is known about children and youth. Recent work found age-related differences in the geography of pedestrian-MVCs specifically related to Toronto’s urban versus inner suburban neighbourhoods, suggesting that urban form and built environment risk factors vary with age [15]. A systematic literature review examining the built environment features associated with safe walking in children found that the majority of traffic design interventions had inconsistent associations with either walking or injury, potentially due to diverse outcomes and built environment measurement [27]. In addition, the majority of studies included in that systematic review were cross-sectional.It is recommended that future research include objective measurements, such as observational counts for walking, and geographic information systems data-based built environment measures. Further, as randomised trials are difficult to implement for traffic interventions, the authors recommended case-control, case-crossover, and quasi-experimental designs with spatial analysis methods. We have studied built environment features associated with child pedestrian-MVCs and walking to school in Toronto and Montreal using environmental audits with cross-sectional [28–31] and pre-post installation quasi-experimental designs [32]. Across these studies, several urban design features (e.g., population density, traffic calming, school crossing guards, one-way streets) have been consistently associated with rates of child pedestrian injuries.

The urban built environment can confer health and health equity benefits (through promoting active transportation) and is an important association of traffic injury, the leading cause of child death. Children differ from adults in both active transportation behaviour and traffic injury risk. The substantial gap in child-specific knowledge can be addressed by this team of researchers and community partners, who build upon their own proven innovative methods. Therefore, the purpose of this research program is to determine how the built environment influences child and youth active transportation and their risk of active transportation injury across different Canadian urban settings.

## Research program objectives

Figure 1illustrates the conceptual linkages between our objectives.

**Fig. 1 Fig1:**
[figure not shown]
Framework for Built Environment and Active Transportation Safety in Child and Youth Activities

### Objective 1

To examine associations between the built environment and child active transportation to school within and across multiple large Canadian centres

### Objective 2

To examine associations between the built environment and child and youth active transportation injuries in multiple large Canadian centresProject 2A: To estimate the associations between the objectively measured built environment and child pedestrian-MVCs and bicyclist-MVCs near schools.Project 2B: To analyse the space-time distribution of pedestrian-MVCs and bicyclist-MVCs to understand the geography of child and youth injury events and risk factors.Project 2C: To estimate the effect of built environment traffic features on pedestrian-MVCs and bicyclist-MVCs using a quasi-experimental design.Project 2D: To estimate the associations between the built environment and child and youth bicyclist-injuries using a case-crossover design.

### Objective 3

To identify implementation strategies for built environment change at the municipal level to encourage active transportation.Project 3A: To identify the facilitators and barriers for implementing built environment change at the municipal level.Project 3B: To develop a built environment implementation toolkit, adapted for different municipalities, in order to promote active transportation and/or prevent child pedestrian and bicycling injuries.

## Methods/Design

### Objective 1

To examine associations between the built environment and child active transportation to school within and across multiple large Canadian centres

### Study design

A cross-sectional design will be used that will include primary data collection of active transportation around schools and data from secondary sources related to the built environment, social and individual factors.

### Location and participants

A sample of 125 elementary schools (depending on the number of eligible schools in the jurisdiction) will be chosen in four urban regions (Montreal, Toronto, Calgary, Vancouver). Regular program elementary schools (typically Kindergarten-Grade 8) will be included. Schools with older grades will be excluded as older students have very different school transportation patterns, in part due to developmental skills and larger attendance boundaries for middle and high schools. Schools focused on special programs such as arts-based curricula, French immersion, and special needs will be excluded as their students travel further and may be more likely to be driven. Eligible schools will be stratified by Walk Score® (related to population density and urban form) and socioeconomic status (SES; After Tax-Low Income Cutoff [AT-LICO]) in order to represent several urban and suburban built environment types and to enable some exploration of active transportation and SES [31, 33]. Local knowledge users may participate in selecting municipalities and schools. Across each selected SES/built environment stratum, the list of schools will be randomly ordered, and schools will be observed in the order of randomization until the maximum sample in each municipality is met.

### Recruitment

Schools will be recruited for participation as per specific school district policies.

### Data collection

Direct observations of active transportation to school will be conducted, as per published methods [28, 29, 34–36]. Two trained observers will count children’s travel mode (e.g., walking, bicycle, scooter, vehicle) to school, complete a site survey, and detail built environment features on road segments near the school. Vehicle speed and volume will be measured using municipal speed tubes. The site survey will include presence of designated drop-off areas and presence of dangerous driving and pedestrian/bicyclist behaviours using a checklist we have used previously [37]. We found high test-retest reliability of these count observations in Toronto (Pearson’s r = .96) [29]. Some covariates will come from the site survey whereas others will be extracted from a spatial database compiling built environment metrics at the school-level using different network distance buffers (e.g., between 500 m and 1.6 km, the most frequent distances in the literature and representing a credible range of child walking distances). Using different buffer distances addresses the modifiable areal unit problem [38–40]. The problem reflects how scale and zoning affects the measurement of the built environment. For example, using a smaller distance buffer may produce unstable results, whereas a larger distance buffer may increase the correlation of different built environment variables (scale effect). A zoning effect exists when different buffer sizes produces dissimilar results [38]. Conducting a sensitivity analysis using different buffer sizes will help inform the accuracy and stability of our results. Metrics to populate objectively measured built environment predictors (3D’s- density, diversity, design) will be calculated from the spatial databases. Each predictor will be assessed within street network based distance buffers around schools:

#### Density

Population density, housing density.

#### Diversity (urban built environment)

Land use diversity index (entropy), park area (% of the total land), date of housing construction, number of recreational facilities.

#### Design

1) **Road infrastructure**: road length, proportion of each road type per zone (arterial, local streets), one-way streets, sidewalks, separated paths, intersection, roundabouts, traffic circles, dead-ends/cul-de-sacs, transit types, transit stops; 2) **Traffic features**: traffic calming devices (e.g. speed bump, corner radius, chokers, diverters), traffic lights and other signage (stops, yield) density, crosswalks, countdown timers; 3) **Socio-demographic context**: deprivation index and proportion of low-income families, immigrant population, linguistic composition; 4) **School context**: school population, number bussed per school, presence of any active transportation to school program, distance allowance to walk to school (dichotomous), presence of school crossing guards, number of other schools within buffer (i.e. private, catholic), date of school construction, school drop off zone (on or off street), vehicle speed, driving behaviours, pedestrian/bicyclist behaviours.

### Data analysis

The primary outcome variable is the observed proportion of students arriving at school via active transportation. Direct observations of active transportation to school will be used to generate a numerator (students observed walking, bicycling, and other active transportation). The denominator is total observed non-school bus student arrivals (walking, bicycling, arriving by vehicle, and other). Children arriving by school bus will be excluded as they typically live further than walking distance. With the school as the unit of analysis, active transportation proportions will be modeled with built environment predictors using multivariable regression [41]. Sensitivity analysis will use different street network buffer distances. Categorical variables will be included in the model representing each of the sites (municipalities) to enable inter-jurisdictional comparisons. Separate models will also be estimated for each municipality.

### Sample size

The target sample size is 125 schools per municipality. Walking rates by school varied from 28 to 98% with a mean of 67% in our previous studies [29]. Using walking rates as an outcome and using built environment predictors we have measured before, only 50 schools per municipality are required to achieve 95% power at a .05 significance level [42]. We target a larger sample required for an injury model.

### Anticipated concerns

We will keep track of characteristics of non-participating schools. However, our experience to date has been positive with schools keen to participate and the number of non-participant schools has been very low (0/24 schools in Vancouver and 8/126 = 6% in Toronto) [29, 34].

#### Objective 2

To examine associations between the built environment and child and youth active transportation injuries in multiple large Canadian centres

#### Project 2A

To estimate the associations between objectively measured built environment and child pedestrian-MVCs and bicyclist-MVCs near schools

### Study design/location/participants/recruitment

This project has the same study design, locations, and participating schools as Objective 1, with the outcome variables being injury-related. Regression models will use the same predictors, with the addition of a variable for observed active transportation to school, estimated from Objective 1.

### Data collection

Collisions involving child pedestrians and bicyclists, ages 4–12, will be extracted from the most recent ten years available of police reported child pedestrian-motorvehicle collisions (MVCs) and bicyclist-MVCs in each municipality. Our partners in each municipality will facilitate the access to these datasets. The file will include the geographical coordinates of the collision, which will be mapped onto school buffers. Collision rates will be estimated using census populations within school buffers. Using 10 years of collision data together generates stable, interpretable child pedestrian collision rates as demonstrated in our published work from Toronto [28].

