### Sample size

Our Toronto work showed an average baseline collision rate of 7.4/10,000 children per year in a sample of 118 elementary schools [28]. Based on this work, traffic calming density had an important association with collision rates with a rate ratio of 1.31 (1.06–1.63) and can be considered an example covariate of interest on which to base our sample size calculations. Traffic calming density had a Poisson distribution and a lambda of 0.44. Therefore, a sample of between 120 and 140 would be required to achieve 95% power at a 0.05 significance level [43]. The existing standard is that there be at least 10 cases for each parameter estimated in a regression model. Our previous model from Toronto had 7 covariates, necessitating at least 70 participant schools. Therefore, by collecting data at up to 125 schools in each of the municipalities, we have sufficient power to detect important rate ratios and the opportunity to compare built environment covariates across geographic locations [42].

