### Location and participants

We will identify the location of newly installed (i.e., within the past ten years) traffic features in four municipalities (Montreal, Toronto, Calgary, Vancouver). Only traffic features with known implementation dates will be included in the study.

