### Data collection

We will use the most recent 10-year period of police-reported traffic collision data. This project will be conducted municipality-wide, not focussed specifically on school zones as in Project 2A. Police reports of pedestrian-MVCs and bicycle-MVCs include the geographical coordinates of the collision, which will be mapped for the four municipalities. Collisions will be assigned to a feature either within a 30 m buffer-zone for point features (e.g. traffic lights) [32, 52–54] or within a 25 m buffer zone if along a roadway segment (e.g. traffic calming) [55–57]. As in other projects, potential built environment predictors will be extracted from the spatial database as described in Objective 1. The potential traffic features include (but are not limited to): 1) Traffic calming (including speed humps, chicanes, pinch points, etc.); 2) Changes in speed limits; 3) Curb extensions; 4) Traffic lights; 5) Stop signs; 6) One-way streets; 7) Level 2, uncontrolled pedestrian crossovers in residential areas; 8) Crossing guards; 9) Dead end roads; 10) Cycle lanes and cycle tracks. Location and installation dates for these built environment features will be obtained from municipality transportation departments where possible.

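### Project 2A sets built environment features with no stated reference date against ten pooled years of collisions, so features installed within that window are credited with collisions that preceded them

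*Protocol article*

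**What the plan says.** **Design and predictors.** Project 2A (Study design/location/participants/recruitment) states: "This project has the same study design, locations, and participating schools as Objective 1, with the outcome variables being injury-related". Objective 1 is cross-sectional. The same paragraph adds: "Regression models will use the same predictors, with the addition of a variable for observed active transportation to school, estimated from Objective 1".

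**When the predictors are measured.** Under Objective 1, Data collection, observers will "complete a site survey, and detail built environment features on road segments near the school" at the school visit. Other covariates will be "extracted from a spatial database compiling built environment metrics at the school-level using different network distance buffers". No reference year is given for that database. The list under Objective 1, Design, mixes items that rarely change, such as road type, with items that can change within a decade, such as traffic calming devices, signals, signage, crosswalks and countdown timers.

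**Outcome.** Under Project 2A, Data collection, collisions at ages 4–12 "will be extracted from the most recent ten years available of police reported child pedestrian-motorvehicle collisions (MVCs) and bicyclist-MVCs in each municipality". The ten years are used together, to obtain stable rates.

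**What 2C knows about timing.** Project 2C, Location and participants: "We will identify the location of newly installed (i.e., within the past ten years) traffic features in four municipalities". Its Data collection section adds: "Location and installation dates for these built environment features will be obtained from municipality transportation departments where possible". Its Anticipated concerns section admits that some dates are hard to get.

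**Timing safeguards in 2A.** The only one, under Anticipated concerns, deals with collision data covering different periods in different cities. It aligns the cities with each other, not the predictors with the outcomes.

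**The concern.** A model of this kind assumes that the recorded feature was in place while the collisions accrued. For a feature installed part-way through the ten years that is false: its earlier collisions are entered as if they had happened with the feature present. The article itself treats such installations as real, since 2C is built on them, yet 2A has no dating of features, no split at installation and no shorter-window analysis.

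At stake are the rate ratios for the devices that a municipality can actually install. A protective device would look weaker than it is. If devices went where collisions were already frequent, it could look harmful. Results from Objectives 1 and 2 feed the local data reports and the toolkit in Project 3B, so a misread 2A association would reach the people who decide on installation.

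**Working it through.** **Inputs from the article:** a ten-year pooled window, predictors measured once, and features of the same kind installed in the same cities within ten years. The article gives no installation dates, so f is assumed and shown as a range. The true rate ratio of 0.70 is an illustration.

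**Plan's own figure.** The sample size of 120 to 140 schools (rate ratio 1.31, Poisson covariate with mean 0.44, 95% power, alpha 0.05) depends on an expected collision count per school that is not given. One standard two-sided formula reaches it with 2.43 to 2.83 collisions per school at zero calming. That is plausible, so the figure is neither confirmed nor refuted. The present point does not depend on it.

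**Step 1: dilution, no targeting.** Take a present/absent feature, a constant underlying rate and child population, and comparison schools that never have the feature. With f the share of the window with the feature in place:

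pooled RR = (1−f) + f × RR

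| Installed after year | f | Pooled RR for a true 0.70 |
|---|---|---|
| 3 | 0.7 | 0.3 + 0.7×0.70 = 0.79 |
| 5 | 0.5 | 0.5 + 0.5×0.70 = 0.85 |
| 8 | 0.2 | 0.8 + 0.2×0.70 = 0.94 |

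The estimate moves towards 1, and further the later the installation. A density covariate will not follow this formula exactly, but the source of the error is the same.

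**Step 2: placement where collisions were already high (assumption).** The article gives no placement rule. Suppose chosen sites have an underlying rate k times that of other sites throughout the window. Then:

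pooled RR = k × [(1−f) + f × RR]

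| Installed after year | k = 1.3 | k = 1.5 | k at which a true 0.70 crosses 1 |
|---|---|---|---|
| 3 | 1.03 | 1.19 | 1/0.79 = 1.27 |
| 5 | 1.11 | 1.28 | 1/0.85 = 1.18 |
| 8 | 1.22 | 1.41 | 1/0.94 = 1.06 |

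A simulation in which sites are chosen on a noisy five-year collision count gives the same message. Its assumptions are 0.32 collisions per area-year, gamma shape 2, 30% of areas chosen and installation in year 5. A true 0.70 appears as 2.74 to 1.13 as the noise SD in the selection rule goes from 0.5 to 8 collisions. The size therefore depends on how strong the targeting was, which the documents do not tell us. No single reversed figure should be quoted.

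**The case against.** **The programme already divides the work.** 2A is to estimate associations, while 2C is to estimate effects before and after installation with each site as its own control. This stands in part. It is why 2C should be the source for dated devices, and why 2A need not be rebuilt. It does not remove the bias: an association with a feature still needs outcomes from the time the feature was there, and the article nowhere limits how 2A results for such devices are to be read.

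**Most predictors are not affected.** Density, land use and road type change slowly. This stands and limits the point to changeable features. It also stands that measurement at the time of the visit is explicit only for the site survey. For the spatial database it is inferred from the missing reference year and the cross-sectional design. An earlier reference year would misclassify later installations instead.

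**Ten years were chosen for stability.** This stands, and is a reason to keep the ten-year model rather than replace it with a short window.

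**Stronger readings that a reader might infer.**
- That many of the 2A features were installed in the window. 2C gives no count or share.
- That the plan's own estimate already shows reverse causation, because "traffic calming density had an important association with collision rates with a rate ratio of 1.31". That figure comes from earlier Toronto work that is not at hand. The article does not say when calming was measured there, and confounding by traffic or by exposure would give the same sign.
- That 2A's power collapses. The 1.31 is itself an association from the Toronto work that the article also cites for ten-year pooling, so discounting it again could count the dilution twice.
- That 2A and 2C will contradict each other. They could, but this is not established.

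**Conclusion.** The concern holds for predictors that changed within the collision window. For these, 2A as described pulls the rate ratio towards 1 when placement is unrelated to collisions: a true 0.70 becomes 0.79, 0.85 or 0.94 for installation after year 3, 5 or 8. This is arithmetic, given a constant underlying rate and the assumed installation years. Reversal of direction is possible but conditional on targeted placement, and its size cannot be fixed from the documents. The number of affected features is likewise unknown. The rate ratio of 1.31 is not evidence of the mechanism, and the sample size is not called into question here. The change should be made before the 2A analysis, because the dates that would reduce the error are already being sought for 2C.

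**What to change.** 1. Keep the ten-year model and state the reference date of each predictor, including those from the spatial database.
2. For features with installation dates from 2C, assign collisions and child-years to the period before or after installation: feature status by year, a child-years offset, and allowance for clustering by school. Do not add the pre-installation collision count as a covariate. Those collisions are already part of the outcome, and the count is undefined for schools with no installation.
3. For changeable features without dates, add a sensitivity analysis restricted to the most recent years.
4. State that 2A associations for devices installed within the window are not to be read as effects, and refer to 2C for those. This is needed even after step 2, because lasting differences between targeted and other sites remain in a between-school comparison.

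**Cost:** some data restructuring and re-use of the 2C dates. Dates will exist only for some features, so alignment will be partial. The shorter-window analysis will have wider intervals, giving up some of the stability for which ten years were chosen.
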